### Covariates

#### CVD-related past and actual perceived stress

Along with the collection of demographic and clinical data and before the questionnaires' administration, patients will be asked to rate how much stressful was the CVD onset and how much stressful is currently the CVD on seven-point scales from (1) not at all to (7) extremely.

#### Writing ratings

Immediately following the last writing session, participants will be asked to rate sixteen items reflecting some aspects of the writings and of the whole writing experience on seven-point scales from (1) not at all to (7) extremely. For example, participants will be asked to rate how emotional and how personally meaningful the essays were.

#### Self-reported mood

Immediately prior to and after each writing session, participants will complete a restricted and "right now" version of the Profile of Mood States (POMS). The scale has 65 affect adjectives rated on a 7-point scale (0 not at all, 7 extremely). As in other studies [17,34,44], we will construct a distress index (Distress) by adding items (e.g., tense, sad) on the Anger, Depression, Tension, Fatigue and Confusion subscales, and we will use the Vigor subscale (e.g., energetic, cheerful) to indicate positive mood.

#### Type D Personality Inventory

The Type D Personality Scale (DS14) is a 14-item scale comprising of two subscales [45]: a seven-item subscale which measures negative affectivity (NA) (e.g., "I often feel unhappy") and a 7-item subscale measuring social inhibition (SI) (e.g., "I often feel inhibited in social interactions"). Respondents rate their personality on a five-point Likert-type scale which ranges from 0 = false to 4 = true (Items 1 and 3 were reverse scored). The NA and SI scales can be scored as continuous variables (range, 0-28) to assess these personality traits independently. Participants who score highly on both NA and SI using a cutoff point of ≥10 on both scales are classified as having a Type D personality.

#### Brief COPE

The Brief COPE is a self-completed questionnaire measuring coping strategies [46]. It is the short form of the most famous 60-item COPE inventory (15 scales with 4 items per scale) and consists of 28 items that compose 14 scales of two items each. Two scales from the full measure were omitted from the brief form because they did not proven useful in previous work or had proven redundant with another scale (Restraint Coping and Suppression of Competing Activities). Three other scales were refocused slightly because they had proven to be problematic in previous work. Positive Reinterpretation and Growth became Positive Reframing (omitting any mention of growth), Focus on and Venting of Emotions became Venting (omitting items that had appeared to relate too closely to experiencing distress) and Mental Disengagement became Self-Distraction. A new scale (self-blame) - not part of the original COPE - was added because of evidence of its importance [46]. Respondents rate each item on a four-point Likert scale which ranges from 1 (*I usually do not this at all*) to 4 (*I usually do right like this*). Items and response options can be converted to a dispositional "coping style" format (the one I used for the present study) and to a situational concurrent format. The first study to establish the validity and reliability of the measure indicated that the a priori scales had adequate internal reliability (from α = 0.82 for Religion to α = 0.54 for Denial) and that the factor structure was generally consistent with that reported for the full COPE [46]. In the present study, the Italian version of the Brief COPE will be used [47] and the 14 scale scores will be computed by averaging the responses to the two composing items.

### Experimental manipulation check

An independent rater not involved in the study and unaware of condition membership will judge whether each writings, randomly ordered, will conform to condition instructions.

### Statistical analysis

Data entry will be conducted by a trained research assistant who will be aware of participants' condition assignment but not of the research hypotheses. Preliminary analyses will be performed to examine assumptions for parametric statistical analysis and baseline equivalence among groups. Given the longitudinal nature of the data (repeated measurements), multilevel modeling analysis in MLwiN 2.21 (Centre for Multilevel Modeling-CMM, University of Bristol) will be used to study health outcomes (physical and mental health, anxiety, depression, post-traumatic growth and number of medical visits for cardiovascular morbidity) as functions of time and experimental conditions. This will allow testing of experimental hypothesis as cross-level interactions between slopes representing time (1^th ^level) coded as 0 for the first (immediately before discharge from hospital) follow-up, as 1 for the second (3-month) follow-up, as 2 for the third (6-month) follow-up and as 3 for the fourth (12-month) follow-up, and a categorical covariate representing conditions (2^nd ^level). We will start with a simple random intercept model (for calculating intra-class correlation [ICC]) and a simple linear growth model, followed by a model with experimental conditions as a time-invariant covariate. We then will structure more complicated models, including models with different within-individual covariance structures and models with nonlinear growth patterns. A critical alpha of 0.05 will be considered for hypothesis testing. Furthermore, on the basis of the best multilevel models structured in the primary analyses, we will explore the moderating effects of some putative covariates at level 2 such as gender, age, coping styles, negative affectivity and social inhibition (Type D personality dimensions), perceived social support and writings ratings. For these secondary explorative analyses no level of significance will be defined. Readers interested in further discussion of analyzing longitudinal data with multilevel modeling analysis are referred to an excellent guide by Kwok et al. [48] as well as a thorough treatment of the issue by Singer and Willett [49].

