### Randomization procedure and blinding

All participants will be randomly assigned to the experimental conditions in a consecutive way. The simple randomization scheme will be generated by using the Web site http://www.randomization.com. Random allocation will take place after the baseline measurements and patients will be blind to condition assignment.

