Participants will be randomized to one of the following four conditions: 1) disease-related expressive writing (DS-EW); 2) standard expressive writing (S-EW); 3) unemotional writing (Sham) and 4) an empty condition not involving a writing task (assessments only). All the active conditions (1, 2 and 3) will consist in four 20-minute writing sessions that will occur during the hospital stay within a 2-week period and that will be scheduled twice a week for each participant.

Writing instructions for the three active groups will be as follows:

At the end of the CR program and before discharge, all participants, including those assigned to the empty control condition, will be re-administered the outcome questionnaires and will be told that they will receive other follow-up questionnaires by mail at 3, 6, 9 and 12 months after discharge from hospital. A form on which to record any medical visits or events over the previous 3 months will be also sent at each participant at each follow-up assessment.

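### The named hypothesis test is a slope difference that starts at discharge, after all writing has ended, so it cannot detect a maintained benefit and turns unfavourable when a benefit fades

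*Protocol article*

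**What the plan says.** The Statistical analysis section plans multilevel growth models for all outcomes and states how the hypotheses are tested: "This will allow testing of experimental hypothesis as cross-level interactions between slopes representing time" and a categorical condition variable. The time variable is "coded as 0 for the first (immediately before discharge from hospital) follow-up", then 1 at 3 months, 2 at 6 months, "and as 3 for the fourth (12-month) follow-up".

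Under Experimental and clinical protocol, the active arms receive "four 20-minute writing sessions that will occur during the hospital stay within a 2-week period". The first post-treatment assessment comes afterwards: "At the end of the CR program and before discharge, all participants" complete the outcome questionnaires again.

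Baseline outcome data exist, since "Random allocation will take place after the baseline measurements". The one use of baseline that the analysis section mentions is this: "Preliminary analyses will be performed to examine assumptions for parametric statistical analysis and baseline equivalence among groups".

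The same section also fits condition as a time-invariant covariate and allows nonlinear growth and other covariance structures. It sets alpha at 0.05 for hypothesis tests.

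**The concern.** The first primary hypothesis under Study design is that disease-related writing improves health outcomes relative to sham and to the empty control. That is a question about level: are treated patients better off? The named test asks something narrower, namely whether the arms diverge after discharge.

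The intervention ends before time 0, so any effect already achieved at discharge goes into the intercept. The Study rationale section announces interest in brief, mid and long-term effects, and the brief effect is exactly what the slope leaves out. The trial could therefore report a null result for a real and lasting benefit, or a coefficient of the wrong sign for a real but fading one.

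**Working it through.** **1. The plan's own power figure.** The Sample size calculation section gives f = 0.4, four arms, two-sided alpha 0.05, power 0.82, 20% dropout, and 92 patients (23 per arm). A one-way ANOVA with 19 per arm (76 completers) has noncentrality f² × N = 0.16 × 76 = 12.16 and power 0.823. Then 19 × 1.2 = 22.8, which rounds to 23 per arm and 92 in total. The figure reproduces, but for a difference among four group means. It says nothing about slopes.

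**2. The slope contrast.** With codes 0, 1, 2, 3 the least-squares slope weights are (−1.5, −0.5, 0.5, 1.5)/5. They sum to zero. For a constant between-arm difference d at all four visits, the expected slope difference is d × 0 = 0. This is algebra and needs no assumption about variances. It also holds for any nonlinear time shape, because a constant difference contains no condition-by-time interaction.

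**3. Assumptions for the percentages (not in the document).** Two arms compared, outcome SD 1, equal within-patient correlation ρ between visits, normal approximation, two-sided 0.05.
- SE of the slope difference: √[(2/n) × (1 − ρ)/5]
- SE of the difference in the mean of four follow-ups: √[(2/n) × (1 + 3ρ)/4]
- With baseline as covariate, (1 + 3ρ)/4 becomes (1 + 3ρ)/4 − ρ².

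**4. Results at n = 19 per arm, ρ = 0.5.** SE(slope) = √(2/19 × 0.1) = 0.103. SE(mean level) = √(2/19 × 0.625) = 0.256.

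| True benefit at codes 0–3 (SD) | Expected slope difference | Slope test significant: favourable / unfavourable | Mean-level test, no baseline |
|---|---|---|---|
| 0.8, 0.8, 0.8, 0.8 | 0 | 2.5% / 2.5% | 88% |
| 0.8, 0.6, 0.4, 0.2 | −0.20 | under 0.1% / 50% | 50% |
| 0 rising evenly to 0.8 | +0.27 | 74% / under 0.1% | 35% |

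For ρ from 0.3 to 0.7, the 88% runs from 95% to 80%, and the 50% unfavourable from 38% to 71%. In 4,000 simulated two-arm trials per scenario, the lasting benefit gave a significant slope in 4.7% and a significant mean level in 86%, or 96% with the baseline score as covariate. The fading benefit gave an unfavourable slope in 48%. Its baseline-adjusted mean level was significant in 69%.

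**5. Results at n = 18 per arm, ρ = 0.6.** SE(slope) = √(2/18 × 0.08) = 0.094.
- Fade from 0.8 to 0.2: z = 0.20/0.094 = 2.12, so 56% unfavourable.
- Steep fade from 0.92 to 0, linear in months (multipliers 1, 0.75, 0.5, 0): slope = 0.92 × (−1.625)/5 = −0.299, z = 3.17, so 89% unfavourable (74% to 99% for ρ from 0.4 to 0.8). The 0.92 is what f = 0.4 implies if one arm differs from three equal arms: 0.4 × 4/√3 = 0.92.
- With a between-patient random-slope SD of 0.2 per step, the variance term becomes 0.08 + 0.04 and the SE 0.115. The two figures fall to 41% and 74%.
- Maintained benefit of 0.5 SD: slope test 5%; mean level 43% unadjusted and 73% with baseline adjustment (67% to 91% for ρ from 0.4 to 0.8). The variance ratio from adjustment is (0.70 − 0.36)/0.70 = 0.49.

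**The case against.** The strongest reply is that the plan also fits condition as a time-invariant covariate. Without the interaction, that term is an average level difference between arms. With the interaction, coding discharge as 0 makes it the difference at discharge. In the lasting 0.8 SD scenario of step 4 its power is 0.76. This stands: a reader might infer that the planned models cannot show an early benefit at all, and that is not so. What remains is that the article attaches the hypotheses to the interaction and none to the condition term. An impression of harm is thus confined to the sign of the named test, read without the condition term beside it.

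Three other stronger readings are not supported.
- A reader might infer that the primary tests are taken from whichever model fits best. The mention of best models governs only the exploratory moderator analyses, for which no significance level is set.
- A reader might infer that leaving out baseline biases the comparison. In a randomised comparison of levels it costs precision only. Under a slope test it also leaves the change from before to after writing outside the test.
- A reader might infer that baseline adjustment is ruled out. The time codes exclude baseline as an occasion. As a covariate it is merely not named, and a condensed article may leave that to a fuller plan.

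The percentages also depend on scenario. The 89% needs a fall all the way to zero and no random-slope variance, and a benefit that grows after discharge would be detected. The trial calls itself partly explorative, yet it still tests hypotheses at 0.05.

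**Conclusion.** The point holds in this form: the test the article names does not answer the question it poses. For a maintained benefit the expected slope difference is exactly zero and rejection stays at 5%, whatever the size of the effect; the zero expectation rests on no variance assumption. For a fading benefit the sign is unfavourable. The chance that it is significant is roughly 40% to 56% for a fade from 0.8 to 0.2 SD at correlations of 0.5 to 0.6, the lower end allowing for random-slope variance. It is up to about 89% for the steep fade at correlation 0.6. These figures assume 18 to 19 completers per arm and SD 1. The stated power of 0.82 applies to group means and does not carry over to the slope test. Because this changes what the trial can conclude, it should be corrected before analysis.

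**What to change.** Name as the primary hypothesis test the between-arm contrast in level, either at one named follow-up or averaged over the follow-ups. Adjust it for the baseline value of the same outcome, or enter baseline as the first occasion and test change from it. Keep slope and nonlinear growth differences as secondary descriptions of how the effect evolves. State which hypothesis each reported coefficient tests.

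The choice of covariance structure is optional here, and so is whether to keep the preliminary look at "baseline equivalence among groups".

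The cost is a change of wording in the analysis section. Baseline scores are already collected, so no visit, questionnaire or patient is added.

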## Methods

### Study design

A four-arm randomized controlled clinical trial with four follow-up assessments (immediately before discharge from hospital, 3 months, 6 months and 12 months after discharge) will be carried out in order to test the following primary hypotheses/outcomes: 1) a modified disease-related expressive writing intervention is effective in enhancing physical and psychological health outcomes (HRQoL, anxiety and depression symptoms, medical visits for CVD-related morbidities) relative to a sham condition in which patients write solely about the facts of their experience with CVD and relative to a control empty condition; 2) the modified disease-related expressive writing intervention is more effective in enhancing physical and psychological health outcomes than a standard expressive writing condition in which patients write about the their deepest thoughts and feelings about the most traumatic or negative event they have experienced in their life. Further hypotheses/outcomes concern post-traumatic growth and are: 1) the modified disease-related expressive writing intervention is effective in enhancing post-traumatic growth relative to sham and control conditions; 2) the modified disease-related expressive writing intervention is more effective in enhancing post-traumatic growth than the standard expressive writing task.

Secondary analyses will be conducted in order to explore the relative efficacy of the writing conditions as a function of patients' gender, age, coping styles, negative affectivity and social constraint (type D personality factors), perceived social support and evaluative ratings of the writing intervention. Accordingly, significant interactions between the experimental conditions and the moderator variables mentioned above are postulated such that, for example, patients low on avoidance will benefit more from expressive writing than avoidant patients and that patients perceiving low social support will benefit more than patients perceiving high social support.

The Medical Ethics Committee of Istituto Auxologico Italiano approved the study protocol.

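### Time is coded 0, 1, 2, 3 for assessments at discharge, 3, 6 and 12 months, so the growth slope is not a rate per unit of time and steady change can look curved

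*Protocol article*

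**What the plan says.** The Statistical analysis section of the protocol article fixes the time variable numerically. It is "coded as 0 for the first (immediately before discharge from hospital) follow-up, as 1 for the second (3-month) follow-up", then "as 2 for the third (6-month) follow-up and as 3 for the fourth (12-month) follow-up". The score is used as a slope: "This will allow testing of experimental hypothesis as cross-level interactions between slopes representing time" and the condition variable. The model sequence starts with a random intercept model "and a simple linear growth model, followed by a model with experimental conditions as a time-invariant covariate". Models with other covariance structures and nonlinear growth follow. The moderator analyses are then built on the best models from that sequence.

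The Study design section places the assessments "immediately before discharge from hospital, 3 months, 6 months and 12 months after discharge", and the Methods part of the abstract also gives follow-up at 3, 6 and 12 months. The Experimental and clinical protocol section differs: patients are to be told of "follow-up questionnaires by mail at 3, 6, 9 and 12 months after discharge from hospital". The time coding has no 9-month occasion.

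**The concern.** The intervals between the four coded occasions are 3, 3 and 6 months, but each is one step on the score. In the three-month unit implied by the first two steps, 12 months would be 4, and 3 would belong to month 9.

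The slope on this score carries the efficacy hypotheses for every longitudinal outcome, including the primary one (SF-12). Two things are at stake. First, a reported slope, or a difference in slopes, cannot be read as change per month or per quarter. Second, the plan moves on to nonlinear growth models. If patients change steadily in calendar time, the coding itself bends the trajectory, and the search for a growth shape may adopt a curve that reflects only the spacing of the visits.

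**Working it through.** **Plan's own figure.** No figure in the article depends on the time coding. The one power figure, 0.82 under Sample size calculation, is used below only as a reference level. It reproduces as a one-way analysis of variance with four groups and f = 0.4. With 19 per arm (N = 76) the noncentrality is 76 × 0.4² = 12.16 and power is 0.823. Adding 20% gives 76 × 1.2 = 91.2, rounded up to 92.

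**Inputs.** Codes x = (0, 1, 2, 3) come from Statistical analysis. Months (0, 3, 6, 12) come from Study design, with the pre-discharge assessment taken as month 0. In three-month units, true time is (0, 1, 2, 4).

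**Step 1: linear fit when change is steady.** Let the true change be 1 unit per three months, so y = (0, 1, 2, 4), with means 1.5 for x and 1.75 for y.

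- Sxy = (-1.5)(-1.75) + (-0.5)(-0.75) + (0.5)(0.25) + (1.5)(2.25) = 6.5
- Sxx = 5 and Syy = 8.75
- slope = 6.5/5 = 1.30 per code step; intercept = 1.75 - 1.30 × 1.5 = -0.2

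| Assessment | Code | True | Fitted | True minus fitted |
|---|---|---|---|---|
| Discharge | 0 | 0 | -0.2 | +0.2 |
| 3 months | 1 | 1 | 1.1 | -0.1 |
| 6 months | 2 | 2 | 2.4 | -0.4 |
| 12 months | 3 | 4 | 3.7 | +0.3 |

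**Step 2: curvature.** The quadratic contrast (1, -1, -1, 1) on y is 0 - 1 - 2 + 4 = 1. The same contrast on squared codes (0, 1, 4, 9) is 0 - 1 - 4 + 9 = 4. The quadratic coefficient is therefore 1/4 = 0.25 per squared code, where the truth is 0. With time as 0, 1, 2, 4 or in months, the straight line fits exactly and the quadratic coefficient is 0.

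**Step 3: efficiency and power.** The correlation of codes with true time is r = 6.5/√(5 × 8.75) = 0.983, and r² = 0.966, so about 3% of the information on a truly linear slope is lost. This takes errors as independent once the random intercept is allowed for. By the normal approximation, power becomes Φ(r(1.96 + z) - 1.96), where z is the normal quantile of the power under month coding:

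- 82% falls to 80.7%
- 80% falls to 78.6%
- 90% falls to 89.0%

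**Step 4: error rates by simulation.** The inputs are illustrative: 19 complete patients per arm, intercept SD 8, residual SD 5 and slope SD 0.15 per month, all assumed, with 4,000 runs. All arms had the same linear slope of 0.5 per month.

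- Slope-by-condition test: rejected in 5.3% of runs with the codes and 5.0% with months.
- Overall time-squared term: significant in 26% of runs with the codes and 5% with months.

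With unequal assumed slopes (0.7, 0.45, 0.2 and 0.2 per month), the slope-by-condition test had power 70.2% with the codes and 72.1% with months. The curvature-by-condition term was significant in 6.5% against 5.1% of runs.

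**The case against.** The strongest reply is that the codes number the follow-up occasions, and the article never says that one step is three months. A reader might infer from Step 1 that the slope is biased upward by 30%. That is not supported. Steady change of 0, 1, 2, 4 averages 4/3 = 1.33 per occasion, close to the fitted 1.30. The 30% appears only if someone labels a code step as three months. This stands. What remains is that a rate per occasion, over occasions of unequal length, is not a rate per unit of time.

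Second, the curvature is spurious only if change is linear in calendar time, which the article does not claim. If change slows after a brief intervention, the codes may fit better. For an assumed square-root path (0, 1.73, 2.45, 3.46), the correlation is 0.983 with the codes and 0.951 with months. This also stands, so the distortion is conditional. But the article does not offer slowing as the reason for its coding, and slowing is what the planned nonlinear models can estimate on a real time scale.

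Third, those nonlinear models can absorb much of the misfit. In the example of Step 1, a quadratic on the codes cuts the largest residual from 0.4 to 0.15. The trajectory is then largely recovered, but only by reporting acceleration that did not occur.

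Fourth, all randomised arms share the same codes, so the coding alone creates no difference between arms. This stands in full.

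**Conclusion.** The point holds as a should-fix. The plan states a numeric time score that treats 3, 3 and 6 months as equal, uses it as the slope that carries the hypotheses, and gives no rationale. The slope is therefore not a rate per unit of time. If change is linear in calendar time it is fitted as accelerating, which biases the choice among growth shapes and carries into the moderator analyses. If the arms also differ in slope, part of that difference shifts into the curvature-by-condition term.

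The size is modest: a correlation of 0.983 with months, about 3% of slope efficiency, and 1 to 1.5 power points by the approximation (1.9 in the one simulated alternative). These losses assume change linear in months. The simulated rates also depend on the assumed variances.

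A reader might infer that the primary between-arm test is invalid. It is not: its type I error stayed near 5% under either coding. Nor does the 9-month mailing show that the codes are wrong. It is a separate contradiction about the schedule.

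**What to change.** In Statistical analysis, define time as months since discharge (0, 3, 6, 12) or, equivalently, as 0, 1, 2, 4 in three-month units. State the unit in which slopes will be reported, and fit the planned nonlinear models on that scale so that any slowing is estimated there. The cost is one line, with no change to data collection or sample size. It is best done before the data are analysed, so that the time scale is not chosen after seeing the fit.

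Separately, reconcile the 9-month mailing under Experimental and clinical protocol with the abstract, Study design and Statistical analysis. If that assessment is kept and analysed, enter it at month 9 (code 3, with 12 months as 4). If it is not, remove it from the text.

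Replacing the slope with categorical time is not required. With four arms and four occasions it would turn a slope-by-condition test on 3 degrees of freedom into an interaction on 9, and it would give up the planned growth-model hypothesis.

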### Sample size calculation

Given that no study has yet evaluated the health effects of expressive writing on patients with CVD and considering the small mean effect sizes calculated by Frattaroli in her meta-analysis on expressive writing studies [37], no appropriate and reasonable empirical data are available for calculating the necessary sample size that would allow a high chance to detect a significant difference across conditions. Because of this, the study may be considered partially explorative and a very large sample (the one necessary to detect the small effect sizes obtained by Frattaroli in her meta-analysis) is thus not needed. Hence, calculations were based on the explorative assumption that the effect of expressive writing on coronary patients' health-related quality of life is large (f = 0.4) in accordance to Cohen's classification [38]. We further decided not to make assumptions on sidedness because the expressive writing procedure may also have negative effects in comparison with the control empty group. On the basis of such considerations, a total sample of 92 participants (n = 23 for each condition) is required taking into account a total dropout rate of 20% to detect this large difference with an alpha of 0.05 two-sided and a power of 0.82. Calculations were made with SamplePower (Release 2.0; SPSS, Inc., Chicago, IL).

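### The model whose condition-by-time test decides the primary hypothesis is not fixed, so type I error is not controlled at the stated 5%

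*Protocol article*

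**What the plan says.** All of this is in the Statistical analysis section of the protocol article unless noted.

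- **Test.** Outcomes are modelled as functions of time and condition, with the four assessments coded 0, 1, 2 and 3: "This will allow testing of experimental hypothesis as cross-level interactions between slopes representing time" and the condition variable.
- **Order of models.** "We will start with a simple random intercept model", given there as the means of obtaining the intra-class correlation. A linear growth model comes next, and then a model with condition added.
- **Search.** "We then will structure more complicated models, including models with different within-individual covariance structures and models with nonlinear growth patterns". No candidate list, order or criterion is given.
- **Level.** The next sentence reads: "A critical alpha of 0.05 will be considered for hypothesis testing". Only the moderator analyses are exempt from a significance level.
- **What is carried forward.** The moderator analyses are run "on the basis of the best multilevel models structured in the primary analyses". Model choice is therefore placed inside the primary analysis.

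The Sample size calculation section calls the study partly exploratory, but still plans "with an alpha of 0.05 two-sided and a power of 0.82".

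**The concern.** Each growth form gives a different test of the same hypothesis. A linear form tests whether straight-line slopes differ between arms, a quadratic form adds differences in curvature, and a transformed time scale weights the visits differently. Condition enters before the further covariance and growth forms are built, so the natural reading is that the candidates are compared with condition already in them. A form can then look better because the arms happen to differ under it. Testing that same difference at 0.05 uses the chance finding twice.

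At stake is the meaning of the primary p-value. If the deciding test is settled after the outcomes have been modelled by condition, a result just under 0.05 cannot be read at its nominal level, and a reader cannot tell which test was planned.

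**Working it through.** **1. The plan's own figure.** The stated inputs are four groups, f = 0.4, two-sided alpha 0.05, 23 per arm and 20% dropout. One-way ANOVA power follows from a noncentral F with noncentrality N × f².

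- 19 per arm: N = 76, noncentrality 76 × 0.16 = 12.16, power 0.823.
- 18 per arm: N = 72, noncentrality 72 × 0.16 = 11.52, power 0.799.

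The stated 0.82 is reproduced at 19 per arm, and 76 × 1.2 = 91.2 rounds up to 92. That calculation concerns an ANOVA and does not bear on the model search. It does fix the size of the trial: 23 × 0.8 = 18.4, so about 18 completers per arm.

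**2. Simulation under no condition effect.** The inputs from the article are four arms, times 0 to 3, the condition-by-time test and alpha 0.05. The article gives no covariances, candidate models or criterion, so these are assumptions:

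- True covariance (total-variance units): random intercept with ICC 0.55; random slope with intercept, slope and residual variances 0.55, 0.05 and 0.40; or AR(1) with correlation 0.75.
- Nine candidates: random intercept, random intercept plus slope, or AR(1), each with linear, log or quadratic growth.
- Maximum likelihood fits, with a Wald chi-square test of condition by time on (4 − 1) × 1 = 3 degrees of freedom for linear or log growth and (4 − 1) × 2 = 6 for quadratic.
- One outcome, 18 complete patients per arm, 1,500 trials per setting. The Monte Carlo standard error is √(0.05 × 0.95 / 1500) = 0.6 points near 5% and at most 1.2 points elsewhere in the table.

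Rejection rate in %, by true covariance:

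| How the deciding test is reached | Random intercept | Random slope | AR(1) |
|---|---|---|---|
| One prespecified linear model, correct covariance | 5.5 | 7.0 | 5.9 |
| Covariance and growth form by AIC, no condition terms, then one test | 5.7 | 7.5 | 5.7 |
| Covariance by AIC, linear growth fixed, condition in | 5.4 | 7.7 | 6.4 |
| Covariance and growth form by AIC, condition in | 8.5 | 11.2 | 9.5 |
| Smallest p-value of the nine | 9.7 | 16.7 | 28.2 |

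A second simulation of 600 trials per setting, also with 18 per arm, gave about 5 to 6% for one correct linear model, 5 to 7% for selection without condition terms, and 9 to 11% for AIC selection with condition in.

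**3. Where the excess arises.** Each rule is compared with the one prespecified model:

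- Selection without condition terms: 5.7 − 5.5 = +0.2, 7.5 − 7.0 = +0.5, 5.7 − 5.9 = −0.2 points.
- Covariance selection only: −0.1, +0.7, +0.5 points.
- Growth form also selected, condition in: +3.0, +4.2, +3.6 points.

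Only the last is clearly beyond simulation noise. The part of the first row above 5% is small-sample error of the Wald test and has nothing to do with searching.

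**The case against.** The strongest reply is that the text gives no selection rule, so no error rate follows from it. If growth form and covariance were chosen without looking at condition, the search would cost almost nothing. A condensed article may leave the rule to an analysis plan that is not shown. The section does fix the model family, the time coding, a linear starting form and the tested term, and the study calls itself partly exploratory. Comparing covariance structures is also ordinary good practice: holding to a random intercept with linear growth rejected in 12.9% and 23.4% of null trials when the truth was random slope or AR(1).

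Much of this stands, and it limits the point. Three stronger readings are tempting but unsupported:

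- A reader might infer that the error rate is known to differ from 5%, or to reach 28%. That figure requires keeping the smallest p-value, which the article nowhere proposes. Under AR(1) it is also inflated by badly fitting random-intercept models that a fit criterion would tend to discard.
- A reader might infer that the modelling is done unblinded. The section says that the data-entry assistant knows the allocation. It says nothing about the person fitting the models.
- A reader might infer that the hypothesis is tested with random-intercept standard errors that are too small. The article fits that model for the intra-class correlation.

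The reply does not remove the core. The article is not merely silent: it sets an order with condition entered first, opens the search after that, attaches 0.05, and speaks of a best model arising from the primary analyses. An analysis plan naming one deciding model would have to narrow that procedure. The exploratory label is used to justify the sample size and is not extended to the primary tests.

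**Conclusion.** The point holds in limited form. The procedure as written does not fix which condition-by-time test decides the hypothesis, so type I error is not controlled at the stated 5%. The actual rate cannot be read from the document. With ordinary AIC selection among models that contain condition, it would be about 8.5 to 11%, roughly 1.5 to 1.6 times the rate of a single correctly specified model (8.5/5.5, 11.2/7.0, 9.5/5.9). Selection without condition terms would leave it near that single model's rate.

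These figures rest on the assumed covariances, candidate set and criterion, on complete data for 18 per arm and on one outcome. They show direction and rough size and do not predict this trial's error rate. The weakness lies in choosing the growth form with condition in the model. Choosing the covariance with linear growth fixed is not a material problem. This should be corrected, at moderate priority.

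**What to change.** Before outcome data are examined by condition, adopt one of two routes for the SF-12 physical and mental summary scores.

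1. **Name one deciding model.** For example: condition, time as a category, their interaction, the pre-randomisation score as covariate and an unstructured within-patient covariance, with a random intercept and slope as the stated fallback. The condition-by-time test of that model decides. A contrast at a single visit is optional and not needed for this point.
2. **Name a selection rule blind to condition.** Choose covariance and growth form by a stated criterion from a listed set of models without condition terms, then add condition and test once.

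Under either route, label every other growth and covariance model as sensitivity or exploratory.

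The cost is a few sentences and slightly less flexibility. Baseline questionnaires are already collected before allocation. Categorical time spends (4 − 1) × (4 − 1) = 9 degrees of freedom on the interaction against 3 for linear growth, which loses some power if the true divergence is a straight line. The second route avoids that loss whenever a linear form is selected. Growth-curve exploration can still be reported, without a confirmatory p-value.
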